## Abstract

**Background:**

Patellar tendinopathy is a chronic overuse injury of the patellar tendon that is especially prevalent in people who are involved in jumping activities. Extracorporeal Shockwave Therapy is a relatively new treatment modality for tendinopathies. It seems to be a safe and promising part of the rehabilitation program for patellar tendinopathy. Extracorporeal Shockwave Therapy originally used focused shockwaves. Several years ago a new kind of shockwave therapy was introduced: radial shockwave therapy. Studies that investigate the effectiveness of radial shockwave therapy as treatment for patellar tendinopathy are scarce. Therefore the aim of this study is to compare the effectiveness of focussed shockwave therapy and radial shockwave therapy as treatments for patellar tendinopathy.

**Methods/design:**

The TOPSHOCK study (Tendinopathy Of Patella SHOCKwave) is a two-armed randomised controlled trial in which the effectiveness of focussed shockwave therapy and radial shockwave therapy are directly compared. Outcome assessors and patients are blinded as to which treatment is given. Patients undergo three sessions of either focused shockwave therapy or radial shockwave therapy at 1-week intervals, both in combination with eccentric decline squat training. Follow-up measurements are scheduled just before treatments 2 and 3, and 1, 4, 7 and 12 weeks after the final treatment. The main outcome measure is the Dutch VISA-P questionnaire, which asks for pain, function and sports participation in subjects with patellar tendinopathy. Secondary outcome measures are pain determined with a VAS during ADL, sports and decline squats, rating of subjective improvement and overall satisfaction with the treatment. Patients will also record their sports activities, pain during and after these activities, and concurrent medical treatment on a weekly basis in a web-based diary. Results will be analysed according to the intention-to-treat principle.

**Discussion:**

The TOPSHOCK study is the first randomised controlled trial that directly compares the effectiveness of focused shockwave therapy and radial shockwave therapy, both in combination with eccentric decline squat training, for treating patellar tendinopathy.

**Trial registration:**

Trial registration number NTR2774.

## Background

Patellar tendinopathy (PT) is a chronic overuse injury of the patellar tendon characterised by activity-related anterior knee pain[1]. Actions that require repetitive heavy loading of the knee extensor mechanism as seen in jumping sports like basketball and volleyball are supposed to be the cause, and this is the reason why PT is often referred to as jumper's knee [2]. PT is an injury that can last for years [3]. Several treatment options have been described in the literature, such as rest, anti-inflammatory drugs, physical therapy (eccentric exercises), injections and surgical treatments [4].

Another treatment option for patellar tendinopathy is Extracorporeal Shockwave Therapy (ESWT), a method that was originally used for lithotripsy (kidney stone fragmentation). ESWT uses shockwaves to treat the affected area. A review of the literature concluded that ESWT seems to be a safe and promising treatment for PT, although more research is necessary [5]. The study that showed the most convincing evidence for its effectiveness in treating PT used a combination of ESWT and eccentric training[6]. It seems therefore important to combine these two treatment modalities.

Some years ago shockwave generators were introduced which do not generate focused shockwaves. These generators have a ballistic source that generates radial shockwaves. Cleveland et al. (2007) showed that radial shockwave generators do not generate real shockwaves and that they act only superficially on the tissue [7].

Nowadays radial shockwave generators are often used because they are more affordable than focused shockwave generators. There is however only one study that has investigated the effectiveness of radial shockwave therapy in treating patellar tendinopathy. Lohrer et al. (2002) demonstrated significant effects on pain and function, suggesting that radial shockwave therapy is an effective treatment for patellar tendinopathy [8]. Their study however was non-randomised and had no control group, making it difficult to draw firm conclusions regarding the effectiveness of radial shockwave therapy. Another study by the group directly compared the effectiveness of radial and focused shockwave therapy for treating plantar fasciitis,[9] and that study found a small difference in favour of focused shockwave therapy.

So far no studies have directly compared the effects of focused shockwave therapy and radial shockwave therapy in patellar tendinopathy in one single randomised controlled study. The aim of the TOPSHOCK study is therefore to compare the effectiveness on patellar tendinopathy of both therapies in combination with eccentric decline squat training in a blinded, randomised study.

## Methods/Design

### Design

The TOPSHOCK study (Tendinopathy Of Patella SHOCKwave) is a two-armed randomised controlled trial. The flow chart of the trial is shown in Figure 1. Patients undergo three sessions of either focused shockwave therapy or radial shockwave therapy in combination with eccentric decline squat training. Outcome assessors and patients are blinded as to which treatment is given. Treatment takes place between June 2010 and November 2011. A baseline measurement will be taken before treatment session 1. Measurements will also take place preceding treatment sessions 2 and 3. Sessions are spaced at 1-week intervals. Follow-up measurements are taken at 1, 4, 7 and 12 weeks after treatment session 3. Two weeks after the final treatment session patients start with a home-based training program consisting of eccentric decline squat training.

**Figure 1 F1:**
[figure not shown]
**Flowchart of the TOPSHOCK study**.

The study was approved by the Medical Ethics Committee (Number 2009/322) of the University Medical Center Groningen, The Netherlands. Participants have to provide informed written consent before randomisation.

### Study population

Patients with PT who visit the Center for Sports Medicine of the University Medical Center Groningen and are diagnosed with PT by an experienced sports medicine physician, and who meet the inclusion and exclusion criteria, are invited to participate in the study.

#### Inclusion and exclusion criteria

Patients eligible for inclusion in this study must meet the following criteria: 1. A history of pain in the patellar tendon or its patellar or tibial insertion in connection with training and/or competition; 2. Symptoms for over three months (to exclude acute inflammatory tendon problems and de novo partial ruptures); 3. Age between 18 and 50 (to reduce chances of other osteochondrotic diseases like Sinding-Larsen-Johanson, Osgood-Schlatter and osteoarthrosis); 4. Palpation tenderness of the patellar tendon; 5. A score below 80 on the VISA-P questionnaire (see measurements section) [10,11].

Exclusion criteria for the study are: 1. Acute knee or patellar tendon injuries; 2. Chronic joint diseases; 3. Signs or symptoms of other coexisting knee pathology; 4. Contraindications for ESWT (pregnancy, malignancy, coagulopathy); 5. Knee surgery or injection therapy with corticosteroids in the last three months; 6. Daily use of drugs with a putative effect on patellar tendinopathy in the last year (e.g. non-steroid anti-inflammatory drugs, fluorchinolones), or use of anticoagulants.

### Randomisation

Blockwise randomisation is performed by an independent researcher of another department with a computer-generated randomisation list. This researcher informs the physical therapist who administers the shockwave treatment about the treatment allocation. Patients' allocation will be concealed from the patients and the outcome assessors at all times during the trial.

### Intervention

Both focused and radial shockwave therapy will be given by one experienced independent physical therapist. Shockwave therapy is applied with a shockwave device that has two applicators and can therefore generate both focused and radial shockwaves (Duolith SD1, Storz Medical, Tägerwilen, Switzerland). Both shockwave interventions will be administered without local anaesthesia, since several studies have shown that treatment without anaesthesia is superior to treatment with anaesthesia [12-14].

#### Focused shockwave therapy

Focused shockwave is applied with the focused applicator of the shockwave device. Three sessions will be administered at one-week intervals. Each session consists of 2000 impulses at 4 Hz. The energy flux density is 0.12 mJ/mm^2^, since this corresponds with 2.4 bar on the radial shockwave generator of the used machine (personal communication with manufacturer, 18 May 2010). A fixed energy intensity was chosen instead of a patient guided energy intensity. A patient guided energy intensity may influence the results because one type of shockwave therapy may be more painful compared to the other, therefore leading to a difference in energy intensity level between groups. Rompe et al. (2008) used 2.4 bar for effectively treating insertional Achilles tendinopathy [15], with favourable results and no report of dropouts because of the treatment being to painful. Since PT is often also an insertional tendinopathy the same intensity was chosen in the present study. The patient will be in supine position with the knee slightly flexed. Transmission gel is applied between the applicator and the skin. The applicator is slowly moved around the point of maximal tenderness.

#### Radial shockwave therapy

The procedure for radial shockwave treatment is the same as for focused shockwave therapy, the only difference being that impulses are applied at 8 Hz and the treatment intensity is 2.4 bar.

#### Eccentric decline squat training

Both treatment groups will be given a standard home-based program for tendon training. Peers (2003) showed that combining ESWT with eccentric decline squat training gave positive results [6], therefore this is also applied in the present study. The home program consists of performing squats on a decline board[16]. Three sets of 15 repetitions twice a day for 5 days a week will be prescribed [17]. Performing the exercises takes approximately 10 minutes per day. The physical therapist will give instructions on the home training program during the last treatment session. Patients start with the home program two weeks after the last treatment session and continue until the end of the trial (12 weeks post-treatment). The decline squats should be performed with mild pain (VAS < 4). If pain decreases, load will be increased by adding load in a backpack.

#### Concurrent sports participation and medical treatment

Patients will be allowed to keep on participating in sports activities. If there is an increase in pain in the first 48 hours after treatment the participant will be advised to take paracetamol up to a maximum dose of 3 dd 1000 mg.

### Measurements

#### Baseline measurements

Patients will complete the Dutch VISA-P (Victorian Institute of Sport Assessment) questionnaire at baseline [10,11]. The VISA-P questionnaire is designed to measure severity of patellar tendinopathy. The VISA-P score is the primary outcome variable. Patients will also complete a baseline questionnaire that asks for demographics, sports participation and medical history, knee injuries and previous treatment. Anthropometrics of the participants are also collected. Pain experienced during ADL and sports will be rated on a VAS. Finally, pain during one and during 10 decline squats on a 25° decline board is rated on a VAS.

#### Follow-up measurements

At all follow-up moments (before treatments 2 and 3 and 1, 4, 7 and 12 weeks after treatment) the VISA-P questionnaire is completed. At the 7-week and 12-week follow-up pain VAS score during ADL, sports and functional tests (decline squat) are also collected. At these two moments patients answer a question about subjective improvement and their overall satisfaction with the treatment. A follow-up of 12 weeks was chosen because Peers et al. showed favourable effects of a similar protocol within a 12-week period [6]. Adverse reactions and side effects will also be recorded during the follow-up period.

#### Web-based diary

Every week the patients will record their sports activities, pain during and after these activities, and concurrent medical treatment in a web-based diary.

#### Sample size

Sample size is calculated based on the VISA-P score 12 weeks after treatment. A baseline score of 64 points is expected in symptomatic subjects with an SD of 19 points, based on previous investigations [18]. A difference in the VISA-P score of 15 points at the end of the study (12 weeks) is considered to be clinically relevant. With a power of 80% and an alpha of 5%, 28 tendons per group are needed to detect a difference of 15 points between treatments on the VISA-P questionnaire. Since Peers [6] reported no drop-out of patients because of pain (during or after treatment) in a similar protocol, we do not expect a higher-than-normal drop-out rate.

#### Statistical analyses

Results will be analysed using SPSS version 16 (SPSS, Chicago) according to the intention-to-treat principle. Descriptive statistics will be used to describe the characteristics of the focused and the radial shockwave group and the outcome variables at the evaluation moments. The difference on outcome variables between treatment groups after 12 weeks will be assessed using t-tests. A repeated-measures analysis will be used to determine whether there is a difference on outcome variables between the two groups over time. Analyses will be performed for the primary and secondary variables. A p-value < 0.05 is considered statistically significant.

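### The 12-week comparison that sizes the trial is an unadjusted t-test on observed scores only, under an intention-to-treat label

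*Protocol article*

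**What the plan says.** All references are to the protocol article.

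- **Principle.** Statistical analyses: "Results will be analysed using SPSS version 16 (SPSS, Chicago) according to the intention-to-treat principle".
- **12-week method.** Same section: "The difference on outcome variables between treatment groups after 12 weeks will be assessed using t-tests". No covariate and no imputation is mentioned.
- **Longitudinal method.** Same section: "A repeated-measures analysis will be used to determine whether there is a difference on outcome variables between the two groups over time". The type of model is not named.
- **Data collected.** Follow-up measurements: "At all follow-up moments (before treatments 2 and 3 and 1, 4, 7 and 12 weeks after treatment) the VISA-P questionnaire is completed". With baseline, that makes seven VISA-P scores per patient, six of them before week 12.
- **Sample size.** The calculation is based on the 12-week VISA-P with an SD of 19: "With a power of 80% and an alpha of 5%, 28 tendons per group are needed to detect a difference of 15 points between treatments". The authors do not expect unusually high drop-out. They give no rate and no allowance for loss.

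**The concern.** The comparison that carries the sample size is fixed as a two-sample t-test at one visit. Such a test uses only patients who have a score at that visit, unless missing values are filled in first, and the text does not say that they are. A patient who completes five follow-up questionnaires and misses the last one drops out of the main comparison, although the trial holds six of that patient's scores. The intention-to-treat label does not say how such a patient is kept.

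Two things are at stake. The first is power, because the article states no allowance for loss. The second is bias, if the patients without a 12-week score differ from the others and differ between arms. The trial offers a possible route to this. Treatment is given without anaesthesia at a fixed intensity, and the section on focused shockwave therapy acknowledges that one type may hurt more than the other.

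**Working it through.** **Inputs from the article.** Difference δ = 15 points, SD = 19, power 80%, alpha 5%, 28 tendons per group (Sample size), and six follow-up visits (Follow-up measurements). **Assumed.** Two-sided alpha, equal allocation, one tendon per patient, all rates of missing scores, and the within-patient correlation in step 3.

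**1. The plan's own figure.** The normal formula is n = 2·[SD·(z₀.₉₇₅ + z₀.₈₀)/δ]².

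n = 2·[19·(1.960 + 0.842)/15]² = 25.2, so 26 per group.

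The exact t-test calculation (noncentral t) gives 26.2, so 27 per group. The stated 28 is within two of both, and its power by the t-test is 82.7%. The sample size itself is not in error. One-sided alpha would give 20 to 21 and does not reproduce it.

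**2. Power of the t-test when 12-week scores are missing.** The number analysed per group is 28·(1 − d), with power from the noncentral t at δ/SD = 15/19.

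| Assumed 12-week loss d | Analysed per group | Power |
|---|---|---|
| 0% | 28.0 | 82.7% |
| 5% | 26.6 | 80.6% |
| 10% | 25.2 | 78.4% |
| 15% | 23.8 | 76.0% |
| 20% | 22.4 | 73.3% |

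The planned 80% survives a 5% loss and is missed from 10% upwards.

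**3. Bias when loss depends on earlier scores.** Take no true difference, SD 19 at both visits and an assumed correlation of 0.7 between an earlier visit and week 12. In one arm only, the patients in the lowest fraction q at the earlier visit are lost. The mean of the remaining patients in that arm is then too high by

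bias = 0.7 · 19 · φ(z_q)/(1 − q).

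- q = 10%: 13.3 · 0.1755/0.90 = 2.6 points.
- q = 20%: 13.3 · 0.2800/0.80 = 4.65 points.

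A simulation of the same set-up gave 2.63 and 4.59 points, in agreement within simulation error. Against the 15-point target, 2.6/15 = 17% and 4.6/15 = 31%. When the earlier score was used to predict the missing one, as a likelihood-based model does under missing at random, the bias in the simulation was 0.04 and −0.06 points, which is practically zero.

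The set-up is deliberately one-sided. It shows what the choice of method can cost and does not forecast what this trial will see.

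**The case against.** The strongest case against the point has four parts.

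- **Handling of missing scores may stand elsewhere.** An article commonly leaves imputation to a fuller document, and nothing in the text excludes it. This stands, so silence on imputation is not the finding. The finding is the method that the article does name, which has a better alternative on the same data.
- **Intention-to-treat also means analysis by allocated arm.** A t-test by allocated arm respects that. A reader might infer that the plan contradicts its own principle, but the text does not support so strong a statement. What it leaves open is how a patient without a score enters the comparison.
- **The repeated-measures analysis may already be a mixed model.** A reader might infer a classical ANOVA that deletes every patient with an incomplete series. The article never says so, and its wording covers a mixed model equally well. It would also be wrong to take the sample left by deletion over six visits and put it into the 12-week t-test, which loses only patients missing at week 12. If a mixed model is meant, the plan has two methods for the 12-week question that treat incomplete patients differently, and it does not say which is decisive.
- **Pain-related loss may not occur.** The article cites an earlier study of a similar protocol with no drop-out because of pain, and another at the same radial intensity with none reported. The remark that one type may hurt more is there to justify a fixed intensity. This weakens any expectation of unequal loss. It does not exclude ordinary loss, which the Sample size section itself foresees.

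**Conclusion.** The point holds in limited form. As written, the 12-week t-test is an available-case comparison that ignores the baseline score and five follow-up scores. With assumed losses of 5% to 20%, power falls from 82.7% to between about 81% and 73%. Under one-sided loss that depends on earlier scores, the difference could be off by about 2.6 to 4.6 points. The article gives neither a loss rate nor a correlation, so these figures show a range and do not predict a result.

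The documents do not show that a listwise analysis is planned, that imputation is ruled out, or that loss will differ between arms. The 28 per group reproduces adequately. The change is still worth making. A model with baseline VISA-P should be at least as precise as the unadjusted test, and it removes bias from loss that is explained by the scores already collected.

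**What to change.** Make the primary 12-week result the week-12 treatment contrast from one likelihood-based linear mixed model for VISA-P (SPSS MIXED):

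- patients analysed by allocated arm;
- all available follow-up scores as outcomes;
- treatment, visit, treatment-by-visit and baseline VISA-P as fixed effects.

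This also settles what the repeated-measures analysis is. The unadjusted t-test can stay as a supporting analysis. State openly that a patient with no follow-up score still contributes no outcome data to this model. Add one sensitivity analysis that covers such patients and those lost because of pain or lack of effect.

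The cost is some rewording of the Statistical analyses section and slightly more analysis work, with the same visits, data, software and sample size. The model relies on missing at random, which the data cannot confirm, and the sensitivity analysis is there for that reason.

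### The 12-week VISA-P comparison is an unadjusted t-test although baseline VISA-P is available for every patient

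*Protocol article*

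**What the plan says.** The Baseline measurements section states "The VISA-P score is the primary outcome variable", and the Sample size section states "Sample size is calculated based on the VISA-P score 12 weeks after treatment". Together they make the 12-week VISA-P the endpoint that the trial is built on, although no analysis is itself labelled primary.

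For that endpoint, Statistical analyses says "The difference on outcome variables between treatment groups after 12 weeks will be assessed using t-tests". The section appears twice in the article with the same text, and neither copy names a covariate. The next sentence adds a second analysis: "A repeated-measures analysis will be used to determine whether there is a difference on outcome variables between the two groups over time". It does not say whether baseline enters that model as a covariate or as one of the repeated outcomes.

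The baseline value exists for everyone. The article says "Patients will complete the Dutch VISA-P (Victorian Institute of Sport Assessment) questionnaire at baseline", and the inclusion criteria require "A score below 80 on the VISA-P questionnaire". Pain VAS scores for ADL, sports and decline squats are also taken at baseline. The Randomisation section describes blockwise allocation and mentions no stratification by baseline severity.

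**The concern.** A patient's starting score on the same questionnaire is likely to be among the better predictors of the 12-week score. A raw comparison of 12-week means leaves the variation explained by baseline in the error term, so the interval is wider and the power lower than the collected data allow.

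The same loss can be seen from the estimate's side. With about 28 per group and no stated stratification on severity, the groups can differ noticeably at baseline by chance. A raw difference keeps that imbalance in proportion to the baseline slope; an adjusted difference removes it. Over repeated randomisations this is random error, not bias, and the t-test's standard error already includes it. It still affects how the one observed result is read against a 15-point target.

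The article does not leave this choice open for a later plan. It names a method, and that method as written makes no use of baseline.

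**Working it through.** **Inputs from the Sample size section.** "A baseline score of 64 points is expected in symptomatic subjects with an SD of 19 points"; "A difference in the VISA-P score of 15 points at the end of the study (12 weeks) is considered to be clinically relevant"; power 80%, alpha 5%, 28 tendons per group. Assumed here: a two-sided test, one independent observation per tendon, SD 19 also at 12 weeks, and complete data. The correlation r between baseline and 12-week scores is not in the article, so a range of 0.3 to 0.7 is used.

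**1. The plan's own figure.**
- Normal approximation: n = 2 × [19 × (1.96 + 0.84) / 15]² = 25.2, so 26 per group.
- Exact two-sided t-test: 26.2, so 27 per group.
- A one-sided test would need only 20 or 21.

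The stated 28 is therefore reproduced closely, on the basis of an unadjusted comparison with the raw SD. Sample size and t-test agree with each other.

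**2. The t-test at 28 per group.** SE = 19 × √(2/28) = 5.08. The 95% half-width is 2.005 × 5.08 = 10.2 points, and power for 15 points is 83%.

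**3. With baseline as covariate.** Residual SD = 19 × √(1 − r²); SE = residual SD × √(2/28); half-width = t(53 df) × SE; equivalent unadjusted n = 28 / (1 − r²).

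| r (assumed) | Residual SD | SE | 95% half-width | Power | Equivalent n per group |
|---|---|---|---|---|---|
| none (t-test) | 19.0 | 5.08 | 10.2 | 83% | 28 |
| 0.3 | 18.1 | 4.84 | 9.7 | 85–86% | 31 |
| 0.5 | 16.5 | 4.40 | 8.8 | 91–92% | 37 |
| 0.7 | 13.6 | 3.63 | 7.3 | 98% | 55 |

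The lower power figure in each range allows for the small cost of estimating the slope when the groups differ by chance at baseline; the upper one ignores it.

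**4. Chance imbalance at baseline.** With a baseline SD of 19, the SE of the difference in baseline means is 5.08, and the chance that it exceeds 5 points in either direction is 32%. If 64 and 19 describe a normal population before the entry limit, cutting it at 80 gives:
- standardised limit (80 − 64)/19 = 0.84 and variance factor 0.583;
- baseline SD 19 × √0.583 = 14.5;
- SE 14.5 × √(2/28) = 3.88, and a 20% chance of a gap above 5 points.

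The unadjusted estimate carries slope × imbalance. A 5-point gap moves it by 1.5, 2.5 or 3.5 points at slopes of 0.3, 0.5 or 0.7. The middle figure is one sixth of the 15-point target (2.5/15) and about half of one standard error (2.5/5.08).

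**5. Effect of the entry limit on the gain.** Under the same normal model, a correlation of 0.5 before truncation falls to 0.5 × 0.764 / √(0.75 + 0.25 × 0.583) = 0.40 in the trial, and the 12-week SD falls to about 18.0. The t-test then has about 87% power and ANCOVA about 92%. If the 12-week SD stays at 19 with r = 0.40, ANCOVA gives about 88–89% and a half-width of 9.3, against 83% and 10.2 unadjusted.

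**The case against.** The strongest reply is that nothing is wrong in the strict sense. A t-test on randomised groups holds its 5% error rate, is unbiased over randomisation, and has 83% power against a target of 80%. The imbalance argument and the precision argument are largely one loss described twice. All of this stands, and it is why the point is an improvement and not a claim of invalidity.

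The size of the gain also rests on a correlation that the article does not give. At r = 0.2, power without the slope-estimation cost would be only 84%, and the entry limit of 80 may well lower r. This stands too: the gain may be nearer the low end of the range. If r were close to zero, adjustment would cost about one degree of freedom, so the downside is small.

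The planned repeated-measures analysis could use baseline, since VISA-P is measured then and at six later visits. This helps only in part. The article does not say how baseline enters, and that analysis addresses differences over time, whereas the 12-week difference is expressly given to t-tests.

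Finally, a condensed article often leaves covariates to the full protocol or analysis plan. That would excuse silence about the method. Here a method is named, and it is not one that adjusts for baseline.

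**Conclusion.** The concern holds. The 12-week VISA-P difference is assigned to an unadjusted t-test although the same measure is available at baseline for every patient. The test is valid, and the stated sample size is sound for it.

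The loss is in precision. At 28 per group and SD 19, the interval is ±10.2 points where adjustment would give ±9.7 to ±7.3, and power is 83% where it would be about 85% to 98%, for assumed correlations of 0.3 to 0.7. If the below-80 limit weakens the correlation to about 0.4, the gain is about 5 percentage points of power. All figures assume complete data, and the article gives no numerical drop-out allowance. The change should be made because it costs almost nothing, not because the present analysis would mislead.

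**What to change.** In Statistical analyses, replace the t-test for the 12-week VISA-P by a linear model of the 12-week score on treatment group with baseline VISA-P as covariate, reporting the adjusted mean difference with its 95% confidence interval. A mixed model over the follow-up visits, with baseline as covariate and the 12-week treatment contrast as the named result, would serve equally well and would settle the role of baseline in the repeated-measures analysis. State which analysis is primary, and keep the unadjusted t-test as supportive.

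Apply the same adjustment to the VAS outcomes that have a baseline value (ADL, sports, decline squats).

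The cost is one or two sentences and about one degree of freedom. The data are already collected, the planned software can fit the model, and the 28 per group need not change. Fixing the choice before treatment codes are revealed also rules out a later selection between adjusted and unadjusted results.
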